**A study to assess primaquine treatment guidelines on malaria in south-east Bangladesh**

**PI: [name]**

**Co-PIs: [name], [name], [name], [name], [name], [name]**

**Version 2.1**

| **SYNOPSIS** |  |
| --- | --- |
| **Title** | **A study to assess primaquine guidelines on malaria treatment in south-east Bangladesh** |
| **Protocol Number** | *--to be added--* |
| **Methodology** | Observational Study |
| **Study Duration** | *P.falciparum* patients to be followed for 30 days  *P.vivax* patients to be followed for 30 days |
| **Country** | Bangladesh |
| **Study Centre** | Alikadam |
| **Primary Objective** | - To assess side effects observed following unsupervised PQ treatment in *P. vivax* and *P. falciparum* patients |
| **Secondary Objectives** | - To assess the schizontocidal efficacy of 3 days Chloroquine (CQ) for *P. vivax* - To assess parasite clearance rates in P*. falciparum* patients treated with artemether-lumefantrine (AL) - To determine the risk of haemolysis associated with G6PD activity - To determine the distribution of G6PD activity and genetic variants among malaria patients - To determine parasite related factors that may affect treatment outcome |
| **Inclusion Criteria** | - Age ≥ 12 months - *P. vivax* or *P. falciparum* monoinfection or *P.v.* / *P.f.* mixed infection - Presence of axillary temperature ≥ 37.5°C or history of fever during the past 24 hrs - Ability to swallow oral medication. - Ability and willingness to comply with the study protocol for the duration of the study - Informed consent/assent from the patient or from a parent or guardian in the case of children. |
| **Exclusion Criteria** | - Presence of general danger signs in children aged under 5 years or signs of severe malaria according to the definitions of WHO - Presence of severe malnutrition - Acute anaemia <8g/dL - Regular medication, which may interfere with antimalarial pharmacokinetics - History of hypersensitivity reactions or contraindications to any of the drug(s) tested or used as alternative treatment(s) - A positive pregnancy test or lactating - Severe G6PD deficient patients will be excluded from PQ treatment |
| **Study design** | This study is a prospective observational cohort study actively monitoring the hematologic response, safety and tolerability of routine treatment of *P. falciparum, P. vivax* and mixed malaria infections (*P. falciparum + P. vivax*). The study will be conducted in Alikadam in the Chittagong Hill Tracts (CHT). |
| **Duration of administration** | - *P. falciparum*: supervised AL for 3 days + single dose PQ - *P. vivax*: Supervised CQ for 3 days + unsupervised PQ for 14 days - Mixed infections: supervised AL for 3 days + unsupervised PQ for 14 days |
| **Duration of patient enrolment** | - Six months |
| **Endpoints** | Safety Endpoints:   - Proportion of patients with severe anaemia (Hb<7g/dl) - Proportion of patients receiving blood transfusion - Fractional change in Hb between baseline and day 9,16, 23 and 30 (incl. proportion of patients with >25% drop in Hb between the timepoints) - Proportion of patients with anaemia less than 8g/dl on day 3 and day 9 - Proportion of patients with adverse and serious adverse events   Efficacy endpoints:   - Proportion of patients with any parasitemia on day 1, 2 and 3 after treatment - Proportion of patients with fever on day 1, 2 and 3 after treatment - Recurrence of parasitaemia within 30 days of follow up   Other Endpoints:   - Proportion of patients adhering to 14 days of primaquine treatment in the vivax cohort as measured by Masimo and pill count - Distribution of G6PD activity among the study population - Frequency and type of variants of the G6PD gene within the study population |
| **Date of first patient enrolled** |  |

Contents

[1. Background 5](#_Toc395861878)

[1.1. Local malaria epidemiology and treatment guidelines 5](#_Toc395861879)

[1.2. Study Site 7](#_Toc395861880)

[**1.3.** **Context of project** 9](#_Toc395861881)

[2. Rationale and Aim 9](#_Toc395861882)

[3. Objective 9](#_Toc395861883)

[4. Methods 10](#_Toc395861884)

[4.1. Study Design 10](#_Toc395861885)

[4.2. Inclusion Criteria 10](#_Toc395861886)

[4.3. Exclusion Criteria 10](#_Toc395861887)

[4.4. Study Procedures 11](#_Toc395861888)

[4.4.1. Treatment & sample collection 11](#_Toc395861889)

[4.4.2. Concomitant treatment 15](#_Toc395861890)

[4.4.3. Rescue treatment 15](#_Toc395861891)

[4.4.4. Loss to follow up 15](#_Toc395861892)

[4.4.5. Patient withdrawal and protocol violation 15](#_Toc395861893)

[4.5. Laboratory and test procedures 16](#_Toc395861894)

[4.5.1. Microscopy 16](#_Toc395861895)

# Background

## Local malaria epidemiology and treatment guidelines

Malaria is endemic in 13 out of 64 districts of Bangladesh, representing a population at risk of about 27 million people. The highest rates of malaria in Bangladesh occur in the Chittagong Hill Districts, and *Plasmodium falciparum* (Pf) is the most prevalent species. Recent data from a cross sectional survey in 2009-2012 found a monthly incidence rate of 0.05/1000 individuals for symptomatic *P. vivax* (Pv) infections and 1.16/1000 for symptomatic *P. falciparum*[[1](#_ENREF_1)]. An earlier survey looking at the overall burden of disease (asymptomatic and symptomatic cases) found a prevalence of 14% for all species combined by microscopy and more than 30% positivity by PCR in Bandarban disctrict [[2](#_ENREF_2)]. In this study *P. falciparum* accounted for 58.9%, *P. vivax* for 13.6%, *P. malariae* for 1.8%, and *P. ovale* for 1.4% of all malaria-positive individuals by PCR. The remaining 24.4% were mixed infections[[2](#_ENREF_2)]. Within the district recent data from the Ministry of Health indicates highest rates in the subdistrict of Alikadam. Malaria is seasonal in the Chittagong Hill Tracks, with the peak transmission between May to October[[2](#_ENREF_2), [3](#_ENREF_3)].

**Figure: Map of Bangladesh with districts coded according to malaria endemicity**

[figure not shown]

*Source: [name], Directorate General of Health Services, Bangladesh Ministry of Health and Family Welfare*

Chloroquine (CQ) has been the primary treatment for blood stages of vivax malaria for almost 60 years, however evidence is gathering for its declining efficacy across much of the vivax endemic world[[4-12](#_ENREF_4)]. Understanding the extent and regional distribution of chloroquine resistance (CQR) in vivax malaria is critical to optimize treatment guidelines, and reduce the risk of recurrent malaria.

For several years artemsinin combination therapy (ACT) is recommended by national guidelines for the treatment of *P.falciparum* infection. However resistance to artesunate has been shown in Cambodia[[13-16](#_ENREF_13)] and more recently along the Thai-Myanmar border[[17](#_ENREF_17)]. In Bangladesh Artemisinin resistance has not been described to date, although the last systematic reports were derived from studies performed in 2009 [9].

Primaquine (PQ) is administered in combination with Chloroquine and ACT without prior testing for Glucose – 6 – Phosphate Dehydrogenase (G6PD) deficiency according to national guidelines. Primaquine is the only drug currently available on the market with hypnozonticidal and, in *P.* f*alciparum* gametocidal, properties[[18](#_ENREF_18)], but can cause severe haemolysis in G6PD deficient individuals, one of the commonest enzyme deficiency in humans, known to be protective against *P. vivax* infections [[19](#_ENREF_19)].

**Primaquine Roll Out Monitoring Pharmacovigilance Tool (PROMPT) program**

This proposed study is part of a multi-center study under the umbrella of the Primaquine Roll Out Monitoring Pharmacovigilance Tool (PROMPT) program. Key objective of this program is to assess and identify operational and clinical obstacles associated with roll out of routine primaquine treatment in malaria. The study is currently being conducted in Swaziland and Senegal. The new site is going to be Bangladesh as well as an additional Asian site to be identified in the coming months

## Study Site

*Alikadam* (Town) has an area of 23.32 sq km. The town has a population of 8326; male 59.44%, female 40.56%. Literacy rate among the town people is 37.1%. The town and district is serviced by one government hospital, the ‘Alikadam Upazilla Health Complex’ with a capacity of 31 beds.

(more details: <http://www.mapsofbangladesh.com/Alikadam-Upazila.php>, last accessed on 02.05.2014)

**Map of Alikadam Subdistrict**

*
[figure not shown]
*

Over the last couple of years Alikadam has continuously reported the highest rates of reported and treated malaria infections:

| **Table: Total Malaria 2013 by sub-districts of the Chittagong Hill districts** | | | | |
| --- | --- | --- | --- | --- |
|  | Pf | Pv | MIXED | Grand Total |
| **Bandarban Sadar** | 500 | 11 | 1 | 512 |
| **Alikadam** | 2190 | 142 | 26 | 2358 |
| **Naikongchari** | 1267 | 15 | 13 | 1295 |
| **Ruma** | 678 | 2 | 2 | 682 |
| **Thanchi** | 1084 | 27 | 1 | 1112 |
| **Lama** | 1382 | 82 | 4 | 1468 |
| **Rowangchari** | 1864 | 5 | 0 | 1869 |
| **Sadar Hospital** | 90 | 1 | 0 | 91 |
| **SMO** | 58 | 0 | 0 | 58 |
| Total | 9113 | 285 | 47 | 9445 |

*Source: Ministry of Health and Family Welfare*

In 2013 the hospital has treated a total of 49 P. vivax cases and 432 P. falciparum cases (Ministry of Health and Family Welfare).

- 1. **Context of project**

This project is embedded into the framework of PROMPT (Primaquine Roll Out Monitoring Pharmacovigilance Tool) hosted by the University of California San Francisco (UCSF), USA, and OPRA (OPtimizing the RAdical cure for vivax malaria) hosted by the Menzies School of Health Research (MSHR), Australia, and is facilitated through the International Centre for Diarrheal Diseases, Bangladesh (icddr,b).

## Rationale and Aim

Unpublished data on the prevalence of G6PD deficiency in Bangladesh indicate rates of 20-40% in the local population. Current national guidelines recommend the addition of Primaquine to antimalarial treatment for *P. falciparum* (single dose treatment) and *P. vivax* mono- infections (14days treatment) as well as for *P. falciparum / P. vivax* mixed infections (14 days treatment). In view of lack of available reliable bedside testing primaquine is administered without prior testing of G6PD status. This study aims to assess possible side effects as a result of current national malaria treatment guidelines. To do so we propose an observational study to assess current national treatment guidelines for vivax and falciparum malaria, considering both host and parasite factors that may influence treatment effectiveness.

# Objective

**Primary:**

- To assess side effects observed following unsupervised PQ treatment in *P. vivax* and *P. falciparum* patients

**Secondary:**

- To assess the schizontocidal efficacy of 3 days chloroquine (CQ) for *P. vivax*
- To assess parasite clearance rates in P*. falciparum* patients treated with artemether-lumefantrine (AL)
- To determine the risk of haemolysis associated with G6PD activity
- To determine the distribution of G6PD activity and genetic variants among malaria patients
- To determine parasite related factors that may affect treatment outcome

# Methods

## Study Design

This study is a prospective, observational cohort study actively monitoring the hematologic response, safety and tolerability of routine treatment of *P. falciparum, P. vivax* and mixed malaria infections (*P. falciparum + P. vivax*). The study will be conducted in at a health care facility in Allikadam, in the Chittagong Hill Tracts (CHT), Bangladesh.

## Inclusion Criteria

- Age ≥ 12 months
- *P. vivax* or *P. falciparum* monoinfection or *P.v.* / *P.f.* mixed infection
- Presence of axillary temperature ≥ 37.5°C or history of fever during the past 24 hrs
- Ability to swallow oral medication.
- Ability and willingness to comply with the study protocol for the duration of the study
- Informed consent from the patient or from a parent or guardian in the case of children.

## Exclusion Criteria

- Bodyweight <6kg
- Presence of general danger signs in children aged under 5 years or signs of severe malaria according to the definitions of WHO (Annex III)
- Presence of severe malnutrition^[[1]](#footnote-1)^
- Acute anaemia <8g/dL
- Regular medication, which may interfere with antimalarial pharmacokinetics
- History of hypersensitivity reactions or contraindications to any of the drug(s) tested or used as alternative treatment(s)
- A positive pregnancy test or lactating.
- Severe G6PD deficient patients will be excluded from PQ treatment

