**Table: Maximum amount of venous blood collected on d0 / body weight**

| **Patient’s approximate weight in kilograms** | **Amount (mL)** |
| --- | --- |
| >6 to 7 | 4-5 |
| >7 | 5 |

All participants will be followed daily until day 2 to provide supervised treatment and ensure clinical and parasitological recovery following chloroquine (Pv arm) or artemether-lumefantrine (Pf arm and Pf/Pv arm) treatment.

Thereafter patients (excluding those with severe G6PD deficiency) will be given unsupervised primaquine for 1 dose (Pf arm) or 14 doses (Pv/mix arm) and reviewed again after 7 days (day 9), 14 days (day 16), 21 days (day 23) and 28 days (day 30). All P. vivax and mixed infections will in addition be followed up after 3 and 10 days (day 6 and 12 respectively) to assure the safety of the provided treatment. Any patient developing signs and symptoms indicative of a malarial episode or an adverse event within the follow up period will be asked to re-attend the clinic for an unscheduled visit, where they will be offered clinical management according to local clinic guidelines. A fingerprick will be performed during every follow up and unscheduled visit, 5ml of blood will be collected for every recurring malaria episode (see table below). Information on adverse events will be collected during every visit. Whenever possible a pill count will be performed on day 16.

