## Enzyme activity testing

G6PD activity will be measured using spectrophotometry at the lab maintained by icddr,b for all participants. Samples are transported on a daily basis from the field to the icddr,b lab and results are communicated to the field. A subset of collected samples, tested with spectrophotometry, will be tested with flow cytometry to assess lyonisation at a reference centre capable of performing the respective procedure

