## Expected benefits

Participants will be provided with a thorough physical examination. The outcome of the re-evaluation of national malaria treatment guidelines and the collection of indicative data on the safety of PQ treatment without prior G6PD testing will be of significant benefit to the local population.

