## Potential risks

The study has an observational character: study drugs, treatment regimen and pre-treatment diagnostic tests are identical to national guidelines. Participating in the study does not pose an increased risk compared to standard treatment for the participant.

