***If no***

Principal reason for premature termination:

☐Patient vomited the study drug a second time and received rescue treatment before PQ was given

☐Early Treatment failure before PQ was given

☐Patient found to be severely G6PD deficient and excluded before PQ treatment was given

☐Patient withdrew consent

☐Lost to follow up

☐Death

☐ Other: please specify………………………………………………

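### The protocol says it assesses primaquine given without G6PD testing, but it tests everyone and withholds primaquine from the severely deficient, so its rates describe a screened cohort

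*Protocol*

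**What the plan says.** On what is being assessed, Rationale and Aim describes the guideline: "In view of lack of available reliable bedside testing primaquine is administered without prior testing of G6PD status". It then states the purpose: "This study aims to assess possible side effects as a result of current national malaria treatment guidelines". Expected benefits promises "the collection of indicative data on the safety of PQ treatment without prior G6PD testing". Potential risks says that "study drugs, treatment regimen and pre-treatment diagnostic tests are identical to national guidelines".

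On what is done, Enzyme activity testing says "G6PD activity will be measured using spectrophotometry at the lab maintained by icddr,b for all participants", with results returned to the field. In the case record form (Annex IX) the G6PD result is item 17 on day 2 and the provision of PQ is item 19 on the same day. Informed Consent adds a second consent process once the G6PD result is known, and the schedule table marks consent on day 2 as well as day 0. Exclusion Criteria states "Severe G6PD deficient patients will be excluded from PQ treatment", and Study Procedures repeats it: "Thereafter patients (excluding those with severe G6PD deficiency) will be given unsupervised primaquine".

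The end-of-study page of Annex IX lists, among reasons for not completing follow-up to day 16, "Patient found to be severely G6PD deficient and excluded before PQ treatment was given".

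**The concern.** The policy named in the aim gives PQ to everyone regardless of G6PD status. The cohort that takes PQ here has been tested, re-consented and selected on the result. The Background (Local malaria epidemiology and treatment guidelines) says PQ can cause severe haemolysis in G6PD-deficient people, so the selection removes the patients expected to be at highest risk.

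Two things follow. A low event rate could be cited as evidence on untested PQ, which is what Expected benefits promises, although the patients who matter most for that question were never exposed. And the Potential risks text, which tells ethics committees how the study relates to routine care, is factually wrong about testing. The Sample Size section also plans to pool the primary results with other sites, which would carry the selected estimate forward under the same description.

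**Working it through.** **Statements against procedures**

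| Topic | Stated | Actually planned |
|---|---|---|
| Pre-treatment tests | Same as the guideline, which has no G6PD test (Potential risks; Rationale and Aim) | G6PD assay in all participants, result before PQ (Enzyme activity testing; Annex IX, day 2) |
| Who gets PQ | All, without testing (the guideline under assessment) | Those not severely deficient, after a second consent (Exclusion Criteria; Study Procedures; Informed Consent) |
| Evidence produced | Safety of PQ without prior testing (Expected benefits) | Safety of PQ after testing and exclusion |

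The two columns cannot both stand.

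**Direction.** Let s be the severely deficient share, a the haemolysis risk on PQ in severely deficient patients, and b the risk in the others.

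- Rate under the untested guideline: s·a + (1 − s)·b
- Rate among PQ-treated study patients: b
- Difference: s·(a − b)

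The difference is positive whenever a > b. If withheld patients stay in the denominator with no PQ haemolysis, the study rate is (1 − s)·b, which is lower still.

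The planned relative risk of a >25% haemoglobin drop by G6PD category (Statistical analyses) covers only participants treated with 14 days of PQ. It therefore has no severe category and cannot supply a.

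**Size.** The protocol has no figure to reproduce: the target of about 50 vivax and 160 falciparum cases comes from 2013 case counts, with no expected event rate. It gives 20–40% G6PD deficiency of any degree in the local population, but no severe share and no risks. The following are assumptions:

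- s = 2% to 20%, which is 20–40% deficient times 10–50% of those severe (0.2 × 0.1 = 0.02; 0.4 × 0.5 = 0.20)
- a = 20% to 50%
- b = 1% to 5%

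| s | a | b | Guideline rate | Treated-only rate | Ratio |
|---|---|---|---|---|---|
| 2% | 20% | 5% | 0.02×0.20 + 0.98×0.05 = 5.3% | 5% | 0.94 |
| 5% | 50% | 5% | 0.05×0.50 + 0.95×0.05 = 7.25% | 5% | 0.69 |
| 10% | 20% | 1% | 0.10×0.20 + 0.90×0.01 = 2.9% | 1% | 0.34 |
| 20% | 50% | 1% | 0.20×0.50 + 0.80×0.01 = 10.8% | 1% | 0.09 |

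The first and last rows are the extremes of the range. With all enrolled in the denominator, the second row gives 0.95 × 5% = 4.75%, a ratio of 0.66.

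**Numbers withheld.** For s = 2%, 5%, 10% and 20%, the expected count among 50 vivax patients is 1, 2.5, 5 and 10. The chance of at least one, 1 − (1 − s)^50, is 64%, 92%, 99.5% and about 100%. Among all 210 patients the expected counts are 4.2, 10.5, 21 and 42.

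**What a bound would look like.** Suppose 5 of 50 vivax patients are withheld and none of the 45 treated has an event. The treated-only result is 0/45, with an exact upper 95% limit of 1 − 0.025^(1/45) = 7.9%. For the untested population the extremes are 0/50 = 0% (withheld counted as non-events) and 5/50 = 10%, exact 95% interval 3.3–21.8% (withheld counted as events).

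**The case against.** The strongest reply is that the primary objective concerns side effects after unsupervised PQ and says nothing about absent testing. That stands. A reader might infer that the primary objective cannot be answered, but it can be, in the patients who take PQ. What fails is the aim in Rationale and Aim and the claim in Expected benefits. The exclusion is also openly stated in several places, Expected benefits promises only indicative data, and the error in Potential risks leaves participants with more testing than the guideline gives, not less.

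The size is also open to challenge, and rightly. The severe share and both risks are assumed. The 20–40% figure is for the local population, while the Background describes deficiency as protective against vivax infection, so the counts for 50 vivax patients may be too high. About 160 of the 210 patients receive a single PQ dose, for which no risk is given either.

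A reader might also infer from Annex IX that withheld patients are taken off follow-up and their haemoglobin course lost. The form records why follow-up stopped, if it did; it does not order it to stop. Exclusion Criteria removes these patients from PQ, not from the study, and the Hemoglobin section measures at all follow-up visits. Study Procedures, however, ties the later reviews to patients given PQ. The text is ambiguous and supports neither reading firmly.

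Finally, withheld patients might look like a ready no-PQ comparison group. They differ from treated patients in G6PD status as well as in PQ exposure, so the contrast would be confounded.

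None of this removes the contradiction, and a separate analysis plan could not cure it: no analysis turns a screened cohort into an unscreened one.

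**Conclusion.** The concern holds as a mismatch between the stated aim and the population exposed. Post-PQ haemolysis and haemoglobin-drop rates, and the relative risk by G6PD category, apply only to patients who were screened and not severely deficient. For the untested guideline they are biased downward, given only that severely deficient patients have the higher risk. The second consent may select further, to an extent that cannot be known in advance.

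The size is not determinable from the protocol. Under the assumed ranges the treated-only rate is 0.09 to 0.94 of the guideline rate; if severe deficiency is rare, the shortfall may be small. The withholding itself is not criticised.

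**What to change.** 1. Restate the aim (Rationale and Aim), the expected benefit and the planned conclusion as PQ side effects after G6PD screening, with severe deficiency excluded.
2. In Expected benefits, correct the claim about PQ without prior testing. In Potential risks, correct the claim that pre-treatment tests are identical to the guideline.
3. Report the number withheld from PQ for severe deficiency, by arm.
4. For the main haemolysis endpoints, add a bound for the untested population, counting withheld patients once as non-events and once as events. Label both as extremes, not estimates.
5. Reconcile Exclusion Criteria, Study Procedures and the Hemoglobin section with the end-of-study page of Annex IX on whether withheld patients stay on the scheduled haemoglobin visits.

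The cost is some protocol wording, one extra table and a narrower claim. No change to who receives PQ is proposed.
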